	***Intervention group only***				
	Acceptability: Funder required questions	2			X
	Acceptability of app: uMARS [55]	20			X
	Interview invitation	1			X
Engagement metrics	***Control group only***	Web metrics		X	X
	Number of times factsheets accessed				
	***Intervention group only***				
	App usage (number and time accessing)	App metric		X	X
	Number and type of activities completed	App metric		X	X
	Perceive helpfulness of activities	In-app self-report		X	X
Total # of survey items per group			I = 96	I = 54	I = 92
			C = 96	C = 54	C = 69

Note: I = Intervention group, C = Control group. Each measure is described in detail below.

### Data analysis

2.10

#### Internal pilot phase

2.10.1

An internal pilot phase assessing feasibility will be conducted during the first three months of recruitment, using a Red-Amber-Green (RAG) rating system to evaluate key trial feasibility outcomes: recruitment, retention, and engagement [59]. This structured framework enables early identification of challenges and supports timely adaptations to ensure trial progression, including stopping actions for the trial if thresholds are not met. Importantly, no primary or secondary outcome data will be reviewed during this phase, preserving trial integrity and allowing full use of all collected data if feasibility benchmarks are achieved. The thresholds and associated actions are outlined in Table 3.

**Table 3 tbl3:** Feasibility assessment thresholds and actions.

Domain	Red (Significant Barrier – Immediate Action Required)	Amber (Needs Attention – Adaptive Action Recommended)	Green (On Track – No Action Required)
**Recruitment**	<30 % of target sample recruited within 6 months despite active efforts.	30–50 % recruited within 6 months.	≥50 % recruited within 6 months.
	*Action:* Review study viability with sponsor and HREC; consider pausing to revise recruitment strategy or halting trial.	*Action:* Expand recruitment channels, revise outreach materials, increase institutional partnerships.	
**Retention**	<40 % of participants complete follow-up surveys.	40–60 % complete follow-up surveys.	≥60 % complete follow-up surveys.
	*Action:* Investigate barriers to retention; assess feasibility of continuing; consider additional supports or modified data collection.	*Action:* Use additional automated reminders, explore additional incentives, assess survey burden.	
**Engagement**	<30 % of participants use the app at least once.	30–50 % use the app at least three times.	≥50 % use the app at least three times.
	*Action:* Conduct urgent review of app usability and content; consult with developers; assess feasibility of updates within study timeframe.	*Action:* Explore opportunities for additional push notifications, adjust onboarding, enhance motivational elements, or enhance UX elements.	

#### Main analyses

2.10.2

Changes in the primary and secondary outcomes will be evaluated using generalised linear mixed models (GLMMs), including random intercepts for participants, random slopes for time, and fixed effects for group, time, and their interaction. For zero-inflated outcomes such as suicidal ideation (e.g., a large number of individuals reporting no ideation), model diagnostics will be used to assess the appropriateness of the GLMM approach, with consideration of alternative specifications (e.g., two-part models such as the zero-inflated Poisson model) if indicated [60,61]. Measures of acceptability and iatrogenic effects will be assessed with descriptive statistics. Pearson correlations will explore associations between app engagement and mental health outcomes. Exploratory analyses will investigate potential moderators, including demographics (e.g., gender and country of origin) and emotion regulation, for the primary and secondary outcomes, as well as for the engagement and acceptability measures. Sensitivity analyses will be conducted to assess whether outcome patterns differ as a function of intervention engagement or baseline stratification levels of suicidal ideation.

Interview data will be analyzed using a rapid qualitative coding analysis, drawing on principles of Framework Analysis [62,63]. This method is well-suited to small samples and time-sensitive evaluations, allowing for systematic and transparent interpretation of participant feedback across key domains [63]. A deductive coding framework will be developed based on the study aims (e.g., app acceptability, usability, engagement, and perceived impact), while remaining open to inductive insights raised by participants. Data will be summarised within NVivo to facilitate cross-case comparisons and identification of common themes and divergent experiences. This approach balances rigour and practicality and is commonly used in applied health and digital mental health research. Analysis will begin once all interviews are completed.

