This study will evaluate the effectiveness, acceptability, engagement, and safety of Bud, a co-designed digital suicide prevention app for international students (see Table 1 for a summary of the study aims and hypotheses). The primary aim is to determine whether Bud leads to greater reductions in psychological distress compared to an active control condition. The secondary aims include evaluating whether Bud leads to improvements in suicide-related risk and protective factors, including help-seeking intentions, perceived burdensomeness, sense of belonging, emotion regulation, and suicidal ideation. The study will also assess the app's acceptability, monitor for any iatrogenic effects, and evaluate user engagement using self-report and app-derived metrics. An embedded internal pilot phase will assess the feasibility of trial procedures, with predefined benchmarks for recruitment, retention, and intervention engagement. Interviews will be conducted with a subset of participants to further explore their views on Bud's acceptability, usability, and opportunities for implementation.

**Table 1 tbl1:** Study aims and hypotheses.

Aims	Hypotheses
**Aim 1:** To evaluate the effectiveness of *Bud* compared to an active control condition on psychological distress and suicide-related risk and protective factors	***Primary outcome***
	*H1:* Participants using *Bud* will report greater reductions in psychological distress compared to the control group at post-intervention.

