### Sample size

2.2

The target sample size of 302 participants (151 per group) was determined through an a priori power analysis conducted using the SIMR package in R [41]. We simulated 1000 datasets for a 2 (intervention vs. control) × 3 (T1, T2, T3) repeated-measures linear mixed-effects model—with fixed effects for group, time, and their interaction, random intercepts, moderate correlations, and a nonsphericity correction factor of 1. Specifying a moderate Group × Time interaction (f ≈ 0.25) at α = 0.05, we found that 252 participants (126 per group) would yield ∼80 % power; inflating for an anticipated 20 % attrition rate resulted in a final sample target of N = 302 (151 per group).

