### Randomization

2.7

Participants will be randomly assigned to either the intervention or control group using a stratified block randomization approach with a block size of six. Stratification will be based on participants’ baseline suicidal ideation (SI) levels, as measured by the YSIS-3 [45], to ensure balanced allocation across three predefined strata: no or mild SI (scores 0–3), moderate SI (scores 4–6), and severe SI (scores 7 and above). The randomization sequence will be generated using a R and implemented within REDCap by a researcher independent of participant management, ensuring allocation concealment until assignment. Due to the nature of the intervention, participants cannot be blinded to their group allocation.

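### The primary mixed model leaves baseline K10 free to differ by arm and omits the randomisation stratum, so it gives up precision that data already collected would supply

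*Protocol article*

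**What the plan says.** Section 2.10.2 (Main analyses) gives one model for the primary and secondary outcomes: a generalised linear mixed model with random intercepts for participants, "random slopes for time, and fixed effects for group, time, and their interaction". Section 2.9 and Table 2 place K10 at T1, T2 and T3, so the baseline value enters this model as a response. Neither baseline K10 nor the stratum is named as a covariate.

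Section 2.7 (Randomization) stratifies on baseline YSIS-3 to "ensure balanced allocation across three predefined strata". In section 2.10.2 the strata come up again only in a sensitivity analysis of whether outcome patterns differ between them.

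H1 in Table 1 predicts "greater reductions in psychological distress compared to the control group at post-intervention". Section 2.2 (Sample size) powered a 2 × 3 model "with fixed effects for group, time, and their interaction, random intercepts", with "Specifying a moderate Group × Time interaction (f ≈ 0.25) at α = 0.05", and reports "252 participants (126 per group") for about 80% power, raised to 302 for 20% attrition. The within-person correlation is described only as moderate.

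**The concern.** Allocation depends on the baseline YSIS-3 score, so the T1 survey precedes it, and any difference between arms in T1 K10 is due to chance. A model with a free group effect at T1 ignores this. It estimates the T3 effect as the difference between arms in T3 minus T1, which carries the full noise of the baseline measurement. An analysis that constrains the T1 means to be equal, or adjusts for T1, removes the part of the T3 variation that T1 predicts and subtracts no more noise than it has to.

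Leaving out the stratum also means that the main analysis does not follow the way participants were randomised.

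At stake is efficiency: wider intervals and lower power for the primary comparison than the same participants could give.

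**Working it through.** **Inputs.** From section 2.2: f ≈ 0.25, α = 0.05 (two-sided assumed), 126 per arm before attrition, 151 per arm after, 20% attrition. From section 2.1: visits at 0, 2 and 4 weeks. Assumed because not given: the correlation r (0.3 to 0.8, equal between all visits) and the dropout pattern (10% lost after T1, a further 10% after T2).

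**Reproducing the plan's figure.** Take d = 2f = 0.5 residual SDs and a T1-to-T3 change with variance 2 (in units of residual variance). With 126 per arm:
- SE = √(2 × 2/126) = 0.178
- power = Φ(0.5/0.178 − 1.96) = Φ(0.846) = 0.801

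This gives 252 participants at 80%. The protocol does not state this reading; it is one that returns its number.

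**Variance of the T3 contrast, complete data.** Let σ² be the K10 variance at each visit.
- Baseline free: 2σ²(1−r) × 2/n
- Baseline constrained or adjusted: σ²(1−r²) × 2/n
- Ratio of free to adjusted: 2(1−r)/(1−r²) = 2/(1+r)

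At r = 0.5 the ratio is 2/1.5 = 1.33; at r = 0.7 it is 2/1.7 = 1.18.

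**Power at 126 per arm, complete data.** At r = 0.5 the adjusted SE is 0.178 × √0.75 = 0.154, so power = Φ(3.24 − 1.96) = 0.900. At r = 0.7 it is 0.178 × √0.85 = 0.164, so power = Φ(3.04 − 1.96) = 0.861.

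**Power at 151 per arm with 20% dropout** (exact generalised-least-squares variances for the assumed covariance, same effect):

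| r | Baseline free | Baseline constrained | Variance, constrained / free |
|---|---|---|---|
| 0.3 | 81.5% | 92.8% | 0.70 |
| 0.5 | 80.9% | 89.1% | 0.79 |
| 0.7 | 80.3% | 85.3% | 0.87 |
| 0.8 | 80.1% | 83.4% | 0.92 |

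Moving all the dropout to before T2, or all to after T2, changes these powers by one percentage point or less.

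**If slopes do vary between participants.** Starting from r = 0.5 and adding a random linear slope with variance 0.05, 0.1 or 0.2 of the residual variance per visit step, power with dropout goes from 77.0% to 85.2%, from 73.3% to 81.2%, and from 66.6% to 73.6%. The gain stays at 7 to 8 points.

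**Stratum.** A stratum main effect cancels in T3 minus T1. In a small simulation (39 replicates, indicative only) adding it left the SE of the free-baseline model at 0.177 and lowered that of the constrained model from 0.158 to 0.154, about 2%. In a larger one (4000 trials) the baseline-adjusted SE went from 0.103 to 0.102, about 1%.

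**Random effects.** If time is the three-level factor of section 2.2 and each later visit has its own random slope, the random intercept and two slopes have 6 covariance parameters. The residual makes 7. Three visits supply a 3 × 3 covariance matrix with 6, so that version cannot be identified for a Gaussian outcome. A random intercept with a single linear slope has 4 parameters and can be estimated.

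**The case against.** The strongest reply is that nothing here is an error of validity. A difference-in-change mixed model is unbiased under randomisation and missing at random and holds its type I error. The gain depends on a correlation the protocol does not give, and it shrinks to about 5 points at r = 0.7. The article is condensed, its list of model terms is introduced as what the model includes, and covariates, time coding and contrast may be settled in an analysis plan not shown. The first part stands, and it limits the point to efficiency. The second does not remove it: the article states a specific primary model, and an analysis plan that follows it inherits the loss.

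Four stronger readings are tempting, and the documents do not support them.
- **That the model misses H1.** H1 concerns greater reductions. With categorical time the T3-by-group coefficient is exactly that contrast. With linear time and three complete, equally spaced visits, twice the slope interaction equals it. What the article leaves open is which contrast is primary.
- **That random slopes lose material precision.** When slopes do not vary, adding them raised the simulated SE by about 2% (0.174 to 0.177). When they do vary, leaving them out makes the SE too small.
- **That the analyst will have to change the model after it fails.** This follows only if time is categorical with a slope per visit, and section 2.10.2 does not state the coding.
- **That omitting the stratum breaks the missing-at-random assumption.** T1 K10 is already in the likelihood and carries information on dropout related to ideation. Under assumed values (stratum–K10 correlation 0.5, T1–T3 correlation 0.6, dropout of 15, 30 and 40% by stratum), the bias in the T3 contrast is nil if dropout depends on stratum equally in both arms, and about 0.02 SD if it does so in one arm only.

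**Conclusion.** The point holds as a recommendation on efficiency. The stated model spends precision on estimating a baseline difference that randomisation makes zero in expectation. The excess variance on complete data is 33% at r = 0.5 and 18% at r = 0.7; at the planned size with 20% dropout this is worth about 8 and 5 points of power. The gain is positive for any r below 1. Its size rests on the assumed r, equal correlations, the assumed dropout pattern, and the reading of f that reproduces 252.

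Omitting the stratum is a departure from analysing as randomised, with a cost in SE of only 1 to 2%. The estimate from the planned model is not biased by either choice under the plan's own assumptions.

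**What to change.** For K10 and the other continuous outcomes measured at T1 to T3, restate the main analysis in one of two ways:
- a constrained-baseline model, with T1 as a response and no group difference at T1; or
- a model of T2 and T3 adjusted for the baseline value of the outcome.

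In either form, use categorical visit, group-by-visit terms at T2 and T3, and an unstructured within-person covariance in place of random slopes, which avoids the identifiability question. Add the suicidal-ideation stratum as a fixed effect, and name the group difference at T3 as the primary contrast. The planned sensitivity analysis by stratum can stay.

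The cost is wording only: baseline K10 and the stratum are both recorded before randomisation, and no extra data or participants are needed. The change should be fixed before outcome data are examined.

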### Overall trial design

2.1

This project employs an open-label, parallel-group randomized controlled trial (RCT) stratified by suicidal ideation to evaluate the effectiveness of the Bud app intervention. The trial will be conducted in accordance with the CONSORT (CONsolidated Standards Of Reporting Trials) 2025 Statement. Participants (N = 302) will be randomly allocated to either the Intervention group (Bud app; n = 151) or the active Control group (mental health factsheets; n = 151). Intervention group participants will have access to the Bud app content and features for four weeks. They will be encouraged to use it at least once per week, but may engage with it as much or as little as they choose. Control group participants will receive access to four mental health fact sheets over the same timeframe. All content in both conditions will be delivered in English. Assessments will occur at baseline (T1), two weeks post-baseline (T2), and post-intervention (four weeks post-baseline; T3), enabling the analysis of intervention effects both within and between groups over time.

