#### Intervention condition: Bud App

2.5.1

The Bud App is a self-guided digital intervention to support international students’ mental health and wellbeing. It targets modifiable risk factors, such as stress and social isolation, while strengthening protective factors, including social support and help-seeking behaviours. The app is intended for use across the continuum of psychological distress, from mild stress to heightened emotional states, but is not a crisis intervention tool. Instead, it provides timely, low-intensity support and directs users to crisis services when needed.

Bud was co-designed with international students to ensure that the app reflects the shared challenges and preferences of this population. While not formally adapted for specific cultural or linguistic groups due to the diversity within international student populations, Bud incorporates culturally sensitive design features, such as non-clinical framing (e.g., no use of terms like “diagnosis” or “therapy”), diverse student narratives, and peer-oriented content to reduce stigma and promote accessibility across a range of cultural backgrounds.

Bud's design is grounded in just-in-time adaptive intervention principles [25]. An emotion-tracking feature promotes emotional awareness and recommends contextually relevant coping tools. Core therapeutic content is based on ACT, CBT and DBT approaches, such as reframing cognitive distortions, using temperature-based distress tolerance techniques, practising gratitude, guided breathing techniques, and structured problem-solving [42,43]. The app also includes a brief suicide prevention gatekeeper course, designed to equip users with the skills to recognise and respond to signs of suicide risk in themselves and their peers, aligned with best-practice adaptations for non-Western contexts [30,31].

To normalise help-seeking and reduce mental health stigma, the app also features stories from international students who share their experiences of navigating mental health challenges and seeking support [44]. Lastly, a gamified element is included, where users earn points that contribute to the growth of their virtual ‘Bud’ character. Participants are free to engage with the app in a manner that suits their individual preferences, with optional daily mood check-in reminders through push notifications and flexible access to content.

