### Assessments

2.9

Assessments will be conducted remotely via REDCap (Research Electronic Data Capture [46,47]) at T1, T2, and T3 (see Table 2).A.*Descriptive Information.* Demographic variables collected at baseline (T1) will include age, gender, country of origin, time in Australia, nationality, education level, study area, degree level, self-rated English language proficiency, and current grade point average (GPA). In addition, participants will be asked to report on previous suicide attempts and considerations of attempts (past 12 months), self-harm behaviours (past 12 months), adjustment to university (College Adjustment Questionnaire: CAQ; [48]), and adverse childhood experiences (Adverse Childhood Experiences Checklist: ACEs [49]).B.*Outcomes.* Primary and secondary outcomes will be assessed at T1, T2 and T3.The primary outcome of this study is psychological distress measured with the Kessler Psychological Distress Scale (K10) [50]. This measure has been validated in diverse populations and is widely used in health related research [56]. Secondary outcomes will include key risk and protective factors for suicidal thoughts and behaviours targeted by the app, including help-seeking intentions using the General Help-Seeking Questionnaire (GHSQ [51]); Perceived burdensomeness and belonging using the Interpersonal Needs Questionnaire (INQ [52]); Emotion regulation using the Difficulties in Emotion Regulation Scale Short Form (DERS-SF [53]); Suicidal ideation using the Youth Suicide Ideation Screen–3 (YSIS-3 [57]); and mental health literacy with the Mental Health Learning Scale (MHL-9 [54]) adapted to refer to the interventions rather than school settings. All instruments are brief psychometrically validated tools designed for self-reporting and appropriate for digital intervention studies.C.*Acceptability and Iatrogenic effects.* Acceptability of the intervention will be assessed at T3 in the intervention group using the User Version of the Mobile Application Rating Scale (uMARS [55]) and a single general satisfaction item (e.g., how satisfied were you with the app?). To assess both acceptability and potential iatrogenic effects, participants in both trial arms will complete a custom measure previously used in suicide prevention research [58]. This measure captures perceived acceptability (e.g., whether the app or fact sheets were enjoyable or worthwhile) and potential iatrogenic effects (e.g., whether the content was upsetting or increased suicidal thoughts). Changes in suicidal ideation, along with monitoring of adverse events, will also provide additional insight into potential iatrogenic effects.D.*Engagement.* For the control intervention, the number of times the fact sheets are accessed will be recorded via REDCap. For the Bud intervention group, app usage data will be collected from participants to assess engagement and perceived usefulness of the Bud app. Specifically, this will include the total number of times the app is accessed, the number and type of activities completed, and responses to in-app prompts asking whether each activity was helpful. These metrics will quantify overall dosage and identify which features are most frequently accessed and perceived as most useful by participants. Participants will also have the opportunity to express interest in participating in an interview about their experience with the app.E.*Interview questions.* A subset of participants from the Bud intervention group who express interest will be randomly selected and invited to participate in online qualitative interviews conducted on Microsoft Teams. We will aim to recruit 20 participants. They will receive $30 for participating in an interview and will be asked to reflect on the app's design, usability, technical challenges encountered, and privacy and security concerns related to sharing personal information within the app. Additionally, the interview will explore the app's content regarding cultural appropriateness, relevance to their experiences as international students, their thoughts about how it could best be disseminated to international student populations, and suggestions for improvement.

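### Unadjusted Pearson correlations between self-chosen app use and outcomes partly reflect who uses Bud; adjusting for the T1 value is a minor, free improvement

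*Protocol article*

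**What the plan says.** Main analyses (2.10.2) names the method for relating use to outcome: "Pearson correlations will explore associations between app engagement and mental health outcomes". It mentions no covariate or transformation, and does not say whether the outcome is the T3 score or the change from T1.

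Assessments (2.9, part D) defines engagement for the Bud group mainly by counts: "this will include the total number of times the app is accessed, the number and type of activities completed". It adds: "These metrics will quantify overall dosage and identify which features are most frequently accessed".

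Use is not fixed by the design. Under Overall trial design (2.1), Bud participants "may engage with it as much or as little as they choose". The description of the intervention (2.5.1) says: "The app is intended for use across the continuum of psychological distress, from mild stress to heightened emotional states".

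Baseline values exist for nearly every outcome. Assessments says: "Primary and secondary outcomes will be assessed at T1, T2 and T3". Table 2 shows one exception, the mental health literacy scale, which is marked at T3 only.

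Main analyses also plans a second look at engagement: "Sensitivity analyses will be conducted to assess whether outcome patterns differ as a function of intervention engagement". The model for it is not stated.

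**The concern.** How much a student uses Bud is an outcome of that student's choices and is not randomised. The app is offered at every level of distress and suggests tools in response to tracked emotions, so use may well follow severity, in either direction. Baseline distress can also be expected to predict distress at T3. A Pearson coefficient between use and outcome then contains a component that comes from baseline severity alone.

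The sign of that component depends on a choice the article leaves open. On scales where a high score is bad, suppose more distressed students use Bud more. A correlation with the T3 score is then pushed towards apparent harm, and a correlation with the change score towards apparent benefit. If less distressed students use it more, both signs reverse.

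What is at stake is the reading of a secondary, within-arm result. Because the use metrics are described as dosage, a significant coefficient could be taken as a dose–response finding, or as a safety signal for an app whose aims include showing no iatrogenic effect.

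**Working it through.** The article gives no figure for this analysis, so there is none to reproduce. The check asks how often the stated test would reject if use had no effect.

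**Inputs from the article**
- Bud arm of 151 (Overall trial design) and anticipated attrition of 20% (Sample size): 151 × 0.8 = 120.8, so n is about 121.
- Level 0.05. It is stated for the power analysis only; two-sided 0.05 is assumed for the correlations.

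**Assumed inputs (not in the article)**
- T1–T3 correlation ρ = 0.6, varied from 0.4 to 0.8, with equal variance at T1 and T3.
- Use negative binomial with mean 5 and gamma shape 0.8 (0.3 for heavier skew). The pilot's green threshold, that at least half of participants "use the app at least three times", is compatible with a mean of this order but does not establish it.
- Log use-rate shifts by b = 0, ±0.3 or ±0.5 per SD of baseline severity. This gives a use–baseline correlation r_UB of about 0, ±0.23 or ±0.35.

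**Expected coefficient with no effect of use**
- T3 score: r = r_UB × ρ.
  - 0.231 × 0.6 = 0.139
  - 0.348 × 0.6 = 0.209
- Change score (T3 − T1): r = −r_UB × √((1 − ρ)/2), and √(0.4/2) = 0.447.
  - −0.231 × 0.447 = −0.103
  - −0.348 × 0.447 = −0.156

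**Rejection rate by the Fisher approximation**, P(Z > 1.96 − atanh|r| × √(n − 3)), with √118 = 10.86
- |r| = 0.139: 0.140 × 10.86 = 1.52, so P(Z > 0.44) ≈ 33%.
- |r| = 0.103: 0.103 × 10.86 = 1.12, so P(Z > 0.84) ≈ 20%.

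**Simulation, 10,000 datasets per scenario, ρ = 0.6, use without effect**

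| Use–baseline correlation | Pearson, T3 | Pearson, change | Spearman, T3 | Spearman, change | Partial correlations given T1 (raw, log or ranked use) |
|---|---|---|---|---|---|
| 0 | 5.0% | 4.9% | 5.0% | 5.4% | 5.1–5.2% |
| about ±0.23 | 33% | 20% | 25–26% | 16% | 4.5–4.8% |
| about ±0.35 | 64% | 40% | 54–55% | 33–34% | 4.8–5.1% |

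The mean simulated coefficients (0.138 and −0.103; 0.208 and −0.156 for positive r_UB) agree with the formulas.

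**Sensitivity to ρ**, at r_UB about 0.23: moving ρ from 0.4 to 0.8 takes the T3-score rate from 16% to 53% and the change-score rate from about 29% to 12%. Across all scenarios the partial correlations given T1 reject in 4.4% to 5.3%.

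**A second set of inputs** (4,000 trials; mean use 6, dispersion 0.6; latent use–baseline correlation 0.2, 0.3, 0.4): Pearson with T3 scores rejects in 20%, 39% and 63%. A regression on log(1 + use) with baseline K10 rejects in 5.0% to 5.4%.

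**Skewness on its own**, with use unrelated to baseline: at skewness about 2.0, rejection is 5.0% (T3) and 4.9% (change); at about 3.1, it is 4.8% and 5.3%. With use and outcome both skewed and independent, it is 4.6% to 5.2%.

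**The case against.** The strongest reply is that the article claims nothing causal. It says the correlations explore associations. If use tracks baseline and baseline tracks T3, a marginal association really exists, and Pearson detects it correctly. The rejections above are false only as statements about an effect of use. This stands, and it limits the point to interpretation. It does not remove it, since an association that mixes severity with use tells the reader little about either.

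The article also plans engagement sensitivity analyses of outcomes that are mostly measured from T1, and these could take baseline into account. That is fair, but with no model stated they cannot be assumed to do so. An analysis plan that is not shown may add detail. Even so, a named bivariate correlation can be adjusted only by replacing it.

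A reader might infer three stronger things that the documents do not support:
- **That skewed counts themselves create a false dose–response.** They do not: rejection stays near 5% when use is unrelated to baseline. Skewness lets a few heavy users dominate the coefficient, and Pearson is somewhat worse than Spearman only once confounding is present.
- **That raw counts will be entered and baseline ignored altogether.** The article does not say. A change score would use T1, though it is not an adequate correction.
- **That the trial will report a dose–response effect.** The word dosage describes amount of use. No hypothesis concerns dose–response; H8 covers usage and perceived helpfulness only.

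**Conclusion.** The point holds as a minor one. The stated correlation does not separate use from baseline severity. Under the assumed inputs, a test with no effect of use rejects in about 33% to 64% of trials with T3 scores and 20% to 40% with change scores, in opposite directions. Conditioning on T1 returns this to about 5%.

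The mechanism follows from self-chosen use plus an outcome that persists over four weeks. The size depends on the use–baseline correlation and the T1–T3 correlation, neither of which the article gives. If use is unrelated to baseline severity, the problem vanishes. The 5% after adjustment covers measured baseline severity only; motivation and other unmeasured causes of both use and improvement would remain. The randomised comparison, the primary outcome and the pilot's progression thresholds are untouched.

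**What to change.** In Main analyses, replace the sentence on Pearson correlations with one along these lines: within the Bud arm, each T3 outcome will be regressed on app use (for example log(1 + use)), adjusted for the T1 value of that outcome where it was collected and for the suicidal-ideation stratum; results will be reported as non-causal associations, because unmeasured confounding remains.

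A partial Spearman correlation given T1 is an acceptable alternative. The log or rank form limits the influence of heavy users; the T1 adjustment is what deals with baseline severity, and changing only to an unadjusted Spearman correlation is not enough. For the mental health literacy scale, which has no T1 value, the text should say that this adjustment is not possible.

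The cost is one sentence of analysis wording. No new data, visits or sample size are needed.
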